### Study participants

#### Identification of study participants

Participants will be recruited into the study through advertisements on the clinic’s own website and local advertising that will not refer to the characteristics of the study products. All study participants (smokers and non-smokers) will be sourced from the Hamburg area from the same communities. Adult, healthy participants of either sex and of any ethnic origin will be enrolled. The planned ratio of male to female participants within each subgroup of the smoking groups is between 3:2 and 2:3, that is, an attempt will be made to enrol approximately equivalent numbers of male and female subjects into each subgroup, within these tolerances.

#### Inclusion criteria

The suitability of participants who give informed consent will be assessed according to the inclusion criteria within 28 days before entering the study and verified upon arrival at the clinic for the first in-clinic evaluation period. The universal inclusion criteria are weight of at least 52 kg (men) or 45 kg (women) and body-mass index within the normal range; no relevant clinically abnormal findings on physical examination, electrocardiography, clinical laboratory testing or lung function tests, or in the medical history, as judged by the investigators; the ability to communicate well with the investigators and understand and comply with the requirements of the study; willingness to refrain from consuming alcohol within 72 h before the first day of each in-clinic evaluation (an alcohol breath test result of up to 0.05% alcohol at the start of a visit might be tolerated, at the discretion of the investigators); willingness to refrain from consuming and avoid being in the presence of the cooking of grilled, fried or barbequed food for 48 h before the first day of each in-clinic evaluation; not being pregnant or breastfeeding and using a reliable method of contraception (e.g., abstinence or barrier methods with spermicide from at least one menstrual cycle before the first day of the study until at least one menstrual cycle after the last in-clinic evaluation, surgical sterilsation of self or partner ≥6 months before the study, an intrauterine device in place or hormonal contraceptives started ≥3 months before the study until at least one menstrual cycle after the last in-clinic evaluation), or being postmenopausal with amenorrhea for at least 2 years.

Additional inclusion criteria for the smoking groups are age 23–55 years; being a regular current smoker of a brand of cigarettes with an ISO tar yield of 6–8 mg and a blend style and mechanics similar to brands sold in Germany; having smoked the same brand for a minimum of 6 months and any brand for at least 5 years before screening; smoking of 10–30 cigarettes per day; willingness to switch to an RTP cigarette and to smoke only products provided during the study; and having a urinary cotinine level of >100 ng/mL.

Additional inclusion criteria for the ex-smoking group are age 28–55 years; not having smoked for at least 5 years but having been a regular smoker of 10–30 cigarettes per day for at least 5 years previously; having a urinary cotinine level of <30 ng/mL (inclusive of levels 0 and 1 on the NicAlert™ test, Palico, Rotkreuz, Switzerland) at screening and <100 ng/mL (inclusive of levels 0–2 on the NicAlert™ test) during the study. Additional inclusion criteria for the never-smoking group are age 28–55 years; never having smoked more than 100 cigarettes during his or her lifetime, and none in the previous 5 years; and having a urinary cotinine level of <30 ng/mL (inclusive of levels 0 and 1 on the NicAlert™ test) at Screening and <100 ng/mL (inclusive of levels 0–2 on the NicAlert™ test) during the study.

Documented exceptions to the inclusion criteria may be permitted at the discretion of the investigators, in agreement with the sponsor, providing risks to participants would not be increased and the realisation of the scientific objectives of the study would not be hindered. Occasional use of paracetamol (up to 4 g per day) might be permitted at the discretion of investigators. Should the need arise to take any other medications, investigators should be informed as soon as possible; if safety allows, the need should be reported before medication is started. All medication administered during the study will be documented, either by the participant during ambulatory periods or by investigators during in-clinic evaluations. In the case of other medical complaints, participants should inform the physician in charge of the study. A physician will be on duty during the entire course of the study, although participants will be referred to their personal physician whenever appropriate (e.g., for the treatment of chronic medical conditions).

#### Exclusion criteria

Exclusion criteria may be applied at screening or at any time during the study. The universal exclusion criteria are clinically relevant gastrointestinal, renal, hepatic, neurological, haematological, endocrine, oncological, urological, pulmonary, immunological, psychiatric or cardiovascular disorders or any other conditions that, in the opinion of the investigators, would jeopardise the safety of the participant or affect the validity of the study results; abnormal findings on physical examination, in the medical history, or in clinical laboratory results deemed clinically relevant by investigators; participation in a previous clinical trial within 30 days before entering the study; donation or loss of at least 400 mL blood within 90 days before entering the study; donation of plasma within 7 days before entering the study; acute illness (e.g., upper-respiratory-tract infection, viral infection etc.) requiring treatment within 4 weeks before entering the study; regular use of any nicotine or tobacco products other than commercially manufactured filter cigarettes; self-reported non-inhaling smoking behaviour (drawing of smoke into the mouth and throat without inhaling); observed as being non-inhalers by the clinic staff at first in-clinic evaluation; history of drug or alcohol abuse within 24 months before screening; positive alcohol breath test and/or urine screen for illicit drugs; positive result for HIV or hepatitis; use of prescription or over-the-counter bronchodilator medications (e.g., inhaled or oral β-agonists) to treat chronic conditions within 12 months before entering the study; use of any medications that interfere with the cyclo-oxygenase pathway (e.g., aspirin or ibuprofen) within 14 days before entering the study; use of any prescribed systemic medication within 14 days before entering the study (except for hormonal contraceptives and hormone-replacement therapy); use of any drugs or substances (except tobacco) known to be strong inducers or inhibitors of CYP (cytochrome P450) enzymes within 28 days before entering the study (Table 2); strenuous physical activity (exceeding the participant’s normal activity levels) within 7 days before screening or in-clinic evaluations; pregnancy; and employment or being first-degree relatives to employees of the tobacco, journalism (television and radio), public relations, market research or advertising industries or the clinic.

**Table 2 T2:** **Strong inducers or inhibitors of CYP (cytochrome P450) enzymes**[19]

**INHIBITORS**			
**1A2**	**2B6**	**2C8**	**2C19**
Cimetidine	Thiotepa	Gemfibrozil	Fluoxetine
Fluoroquinolones	Ticlopidine	Montelukast	Fluvoxamine
Fluvoxamine			Ketoconazole
Ticlopidine			Lansoprazole
			Omeprazole
			Ticlopidine
**INHIBITORS**			
**2C9**	**2D6**	**2E1**	**3A4,5,7**
Amiodarone	Amiodarone	Disulfiram	HIV antivirals:
Fluconazole	Bupropion		Indinavir
Isoniazid	Chlorpheniramine		Nelfinavir
	Cimetidine		Ritonavir
	Clomipramine		Amiodarone
	Duloxetine		NOT azithromycin
	Fluoxetine		Cimetidine
	Haloperidol		Clarithromycin
	Methadone		Diltiazem
	Mibefradil		Erythromycin
	Paroxetine		Fluvoxamine
	Quinidine		Itraconazole
	Ritonavir		Ketoconazole
	Doxepin		Mibefradil
			Nefazodone
			Troleandomycin
			Verapamil
**INDUCERS**			
**1A2**	**2B6**	**2C8**	**2C19**
N/A	Phenobarbital	N/A	N/A
	Phenytoin		
	Rifampin		
**2C9**	**2D6**	**2E1**	**3A4,5,7**
Rifampin	N/A	Isoniazid	Carbamazepine
Secobarbital			Phenobarbital
			Phenytoin
			Pioglitazone
			Rifabutin
			Rifampin
			St John’s wort
			Troglitazone

(Adapted with permission from Version 5.0 (http://medicine.iupui.edu/clinpharm/ddis/table.aspx)).

1A2, 2B6 etc = CYP enzyme subtypes.

For the smoking groups an additional exclusion criterion at screening is planning to quit smoking in the next 12 months (although cessation counselling will be available to smoking participants during and at the end of the study). For the non-smoking groups, additional exclusion criteria are smoking at any time during the study and regular exposure to second-hand smoke (e.g., through living in a household or working with smokers).

#### Withdrawal from the study

Participants will be allowed to withdraw from the study at any time. If they do so, they will receive a pro rata stipend. Investigators may at any time withdraw a participant from the study if they deem this action to be in his or her best interest or that of other participants. The end-of-study examination should be undertaken when a participant leaves the study, if he or she agrees, and reasons for withdrawal should be recorded. If patients cannot be assessed because he or she cannot be contacted after non-attendance of a scheduled event, they will be reported as lost to follow-up.

Participants will be informed of the importance of conforming to all requirements of the protocol, but violations might not result in removal from the study, as the sponsor realises that 100% compliance for every participant over the 6 month period of the study is unlikely. Honesty about protocol violations will, therefore, be encouraged. Participants will be asked to record and report at each clinic visit during ambulatory periods instances when they have not adhered to the protocol, or at check in for in-clinic evaluations. Investigators will decide whether non-compliant participants may remain in the study. Although withdrawals or dropouts are not expected to be replaced, the Sponsor will consider replacing participants to maintain the power of the study.

### Study groups

Participants will be assigned to study groups primarily on the basis of whether they are smokers, ex-smokers or never smokers. The demographics for each group will be matched as far as possible (accepting the constraints of the minimum age difference between smokers and non-smokers) i.e. participants’ sex and age will also be taken into account. The assignment of control cigarettes or RTP cigarettes will be kept within cohorts, i.e., all participants in a smoker subgroup will be switched to the same study product at the same time to meet the restrictions posed by the predetermined schedule for the conduct of the study. For practical reasons, including clinic capacity and sample collection, the smoker and non-smoker groups will be further split into two subgroups (Figure 1). Therefore, to ensure enough participants are recruited to all subgroups, that subject availability will be assured and groups will be well matched for age and gender, we have accepted that full randomisation is not possible. Smokers will be recruited and subgroups filled according to order of screening, age, gender and availability at the study start time. Non-smokers will be recruited on the basis of the same criteria in an attempt to match the control group well with the smoker-group demographics.

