### Previous clinical study assessments

The tools to assess exposure to smoke toxicants were examined in two previous clinical studies conducted in Germany and Canada using conventional cigarettes. These studies aimed to assess whether the available techniques could adequately assess human smoke exposure by filter analysis and measurement of biomarkers of exposure (BoE) [9-11]. These enable the exposure tobacco smoke toxicants or their metabolites to be measured in urine, or other biologic matrices. Both studies showed a good correlation between exposure estimates from the two methods, and, in the case of the German study, the methods were senstive enough to detect changes in smoke exposure following a switch to a cigarette with a lower International Organization for Standardization (ISO) tar yield [10].

Technologies used in the RTPs have previously been shown to significantly reduce yields of a range of tobacco smoke toxicants by 10% to 95% compared with typical commercial products with equivalent ISO tar yields [12]. A clinical study of these RTPs, using a short-term (6-week) switching design, determined smoke toxicant exposure by measurement of various BoE in current smokers after they switched from conventional cigarettes to an RTP (ISRCTN 72157335) [13]. This study showed that toxicant exposure was reduced after switching to the RTP, although the prototypes required further development to optimise the reductions and improve acceptability to smokers.

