#### Ambulatory visits

Participants in the smoking groups will visit the clinic on the first day of the first ambulatory period (Figure 1). Smoking subjects will be asked to confirm the ISO tar yield of their usual brand and smoking status of all subjects will be verified by a urine cotinine test. Participants will be given a diet sheet to which they will be asked to adhere during specified times in ambulatory periods (i.e. 48 h before each in-clinic evaluation). Participants will be supplied with cigarettes according to their assigned product (Table 3) and daily consumption rate, plus two packs, and asked to smoke only the supplied brand until their next visit. Smokers will be allowed to smoke *ad libitum*, rather than according to a pre-specified quantity or timetable.

Each participant will be trained how to use an electronic diary in which he or she will be asked to document cigarette consumption, diet, exercise, medications and any other health-related issues on every ambulatory day. Participants will be required to bring the diary to every clinic visit.

Further ambulatory clinic visits will be made on days 31, 62, 95, 124, 144 and 165 (Figure 1). During these visits, diary entries will be checked, any protocol violations (e.g. consumption of cigarettes that were not supplied by the sponsor, significant health-related events or intake of excluded medications) will be assessed and decisions made about further participation in the study. Urine samples will be taken and tested for cotinine. Cigarette butts will be collected for analysis and the numbers of butts will be compared with diary entries and recorded. Participants will be supplied with further study cigarettes (normal daily consumption x number of days, plus two packs) and reminded to smoke only those until their next visit. They will also receive fresh tins to collect cigarette butts. The clinic staff will record information on hard copy case report forms during visits and will later be transcribed into an electronic system.

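### Smoker subgroups are filled without randomisation and without regard to cigarettes per day, so the RTP and control groups can start with systematically different smoke intake

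*Protocol article*

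**What the plan says.** The Study groups section says of allocation that "we have accepted that full randomisation is not possible". Product follows the cohort: "all participants in a smoker subgroup will be switched to the same study product at the same time". Placement is described as "Smokers will be recruited and subgroups filled according to order of screening, age, gender and availability at the study start time", and for matching the groups "participants’ sex and age will also be taken into account". Identification of study participants adds a numerical tolerance for sex: "The planned ratio of male to female participants within each subgroup of the smoking groups is between 3:2 and 2:3". No similar tolerance is given for any other factor.

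The Inclusion criteria admit "smoking of 10–30 cigarettes per day". Under Ambulatory visits, smokers smoke freely, "rather than according to a pre-specified quantity or timetable". No section balances, bands or caps consumption between the RTP and control subgroups.

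Statistical analysis plans an ANOVA for differences between groups. It adds an ANCOVA with cigarettes per day as covariate, on the ground that consumption may shift over time or because of the switch. It does not name a baseline term, and it does not say at which time point the covariate is measured.

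**The concern.** In place of randomisation, the protocol steers who enters each subgroup. That protects only against the factors used in the steering. Consumption is left out, yet the primary endpoints include urinary biomarkers of exposure, salivary cotinine and exhaled CO, which all depend on how much a person smokes. The protocol itself treats consumption as important enough for a covariate analysis.

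Because a whole subgroup receives one product, any link between consumption and screening order or availability falls on one side of the product comparison. A difference in entry intake could then be mistaken for a product effect, or hide one, when switching and non-switching smokers are compared. That comparison belongs to the primary objective and is the basis of the sample size. The documents do not say that such a link exists, and the filling rule contains nothing that would prevent it.

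**Working it through.** **Inputs from the protocol article.** Eligible consumption is 10–30 per day, a ratio of 30/10 = 3. The sample size is 50 evaluable and 70 recruited per smoking group, from a two-sample t-test with alpha 0.05 and 80% power. At the stated attrition of up to 16%, 70 × 0.84 = 58.8 remain, so 50 and 70 bracket the analysed group size.

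**The plan's own figure.** The 50 per group cannot be reproduced, because no effect size or SD is given. Taking the test as two-sided, 50 per group corresponds to a detectable difference of 0.566 SD.

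**Assumptions not in the documents.** SD of cigarettes per day 4–6 (an even spread over 10–30 would give 20/√12 = 5.77); mean 15–20; correlation between consumption and biomarker 0.3–0.5.

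**Step 1: benchmark under true randomisation.** SE of the group difference = SD × √(2/n).
- n = 50, SD 4: 4 × 0.2 = 0.80; 1.96 × 0.80 = 1.57
- n = 50, SD 6: 6 × 0.2 = 1.20; 1.96 × 1.20 = 2.35
- n = 70, SD 4: 4 × 0.169 = 0.68; 1.96 × 0.68 = 1.33
- n = 70, SD 6: 6 × 0.169 = 1.01; 1.96 × 1.01 = 1.99

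The 95% range is about ±1.6 to ±2.4 at 50 per group and ±1.3 to ±2.0 at 70. This is what randomisation would guarantee. It does not estimate the imbalance that the stated filling rule will produce.

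**Step 2: what a given imbalance would do to an unadjusted comparison of levels.** Two cigarettes are 2/20 = 10% to 2/15 = 13% of mean intake. With SD 5, the bias in biomarker SD units is r × 2/5, which is 0.12 for r = 0.3 and 0.20 for r = 0.5. That is 21% to 35% of the detectable 0.566 SD. From the noncentral t distribution at 50 per group:

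| Quantity | r = 0.3 | r = 0.5 |
|---|---|---|
| Type I error (nominal 5%) | 9% | 17% |
| Power if bias opposes the effect (nominal 80%) | 60% | 44% |
| Power if bias favours the effect | 92% | 97% |

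These rates are conditional on a two-cigarette imbalance, which at SD 5 and n = 50 is 2 SE (SE = 1.0), and on the absence of any baseline adjustment.

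**Step 3: what the planned analyses would remove.**
- If the ANOVA response is percent or log change from the pre-switch value, a stable proportional difference in intake largely cancels.
- If the response is the post-switch level without a baseline term, it does not cancel.
- If the ANCOVA covariate is pre-switch consumption, it targets this imbalance.
- If the covariate is post-switch consumption, it may itself have been changed by the product, and adjusting for it can remove part of the product effect.

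The Statistical analysis section does not settle which of these applies. Its stated reason for the ANCOVA points towards a post-switch value.

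**The case against.** The strongest reply is that the design already contains protection. All smokers use the same commercial product on days 1–14 (Table 3). The pre-switch visit has two 24 h urine collections and repeated exhaled CO and salivary cotinine (Table 4). Switchers are compared with themselves, and the primary objective is to assess changes, descriptively. A stable difference in entry consumption would be visible at that baseline and would mostly drop out of a change analysis. This stands and reduces the likely harm considerably.

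Three stronger readings are tempting and are not supported.
- A reader might infer that the between-group ANOVA is on raw levels. The article says that group levels will be computed at baseline, midpoints and end, and leaves the response variable open.
- A reader might infer that the ANCOVA uses consumption during the study. That is the likelier reading of its rationale, but no time point is given.
- A reader might take the chance ranges in Step 1 as the size of the defect. They are ordinary sampling variation, which a randomised trial without stratification would share and which the t-test error already covers. With an even spread over 10–30, the expected absolute difference at 50 per group is only about 1.15 × 0.80 = 0.9 cigarettes per day.

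Nor can the 10% to 95% yield reductions in the Background serve as a yardstick. They describe technologies across a range of toxicants, not this study's RTP.

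The reply does not show that consumption is balanced anywhere, or that a simple consumption band would be unworkable. An analysis plan written before database closure comes too late to change who entered which subgroup.

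**Conclusion.** The point holds in a limited form. The filling rule omits a known, strong determinant of the primary exposure biomarkers in a design that relies on that rule instead of randomisation. The groups can start with systematically different intake; nothing in the document shows that they will. The existing protections limit the consequence but do not clearly remove it, since the baseline term and the timing of the covariate are both left open.

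The size of the imbalance cannot be derived from the documents. Under the assumed SD of 4–6, randomisation would hold it within about ±1.6 to ±2.4 cigarettes per day at 50 per group (95%), and the stated rule offers no comparable bound. The error rates in Step 2 show sensitivity under an unadjusted analysis and are not a forecast. The change is worth making because it is cheap and has to be made before recruitment.

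**What to change.** In Study groups, add a screening cigarettes-per-day band to the filling factors, for example 10–19 and 20–30. State a tolerance between the RTP and control groups, in the manner of the existing sex ratio. The band can be balanced on its own and need not be crossed with sex, which keeps the number of cells small.

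In Statistical analysis, state that the between-group comparison uses the pre-switch biomarker value and pre-switch cigarettes per day as covariates. If an analysis with post-switch consumption is kept, label it as separate, because it may adjust away part of the product effect.

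Consumption is already established for eligibility, so no new data are needed. The cost is that some screened smokers may have to be placed in another subgroup, within the limits of clinic capacity and participant availability that led to the present rule.

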**Figure 1 F1:**
[figure not shown]
Study design and scheduled events.

The study events will be scheduled to avoid as far as possible overlap of subgroups for in-clinic evaluations; non-smoking subgroups will never be resident in the clinic at the same time as any smoking subgroup.

